## Abstract

**Simple Summary:**

Multiple myeloma is a bone marrow cancer that often causes bone pain, but little is known about the pain characteristics and mechanisms in this condition. This clinical study aims to: 1. characterize the type, location and intensity of pain in myeloma patients, and its effect of quality of life, and 2. investigate whether the nerve fibers in the bone of myeloma patients are altered. We will also explore whether pain intensity is correlated to blood indicators of inflammation or bone damage. Study results will help identify the mechanisms of myeloma-induced bone pain, allowing the development of new analgesics for these patients.

**Abstract:**

Multiple myeloma (MM) is a bone marrow neoplasia that causes bone pain in 70% patients. While preclinical models of MM have suggested that both nerve sprouting and nerve injury may be causative for the pain, there is a lack of clinical data. Thus, the primary aims of this clinical study are: (1) to provide a deep characterization of the subjective experience of pain and quality of life in MM patients; (2) to investigate disturbances in the bone innervation of MM patients. Secondary aims include exploring correlations between pain and serum inflammatory and bone turnover biomarkers. In a prospective, observational study (clinicaltrials.gov: NCT04273425), patients with suspected MM requiring a diagnostic iliac crest biopsy at Sheffield Teaching Hospital (UK) are invited to participate. Consenting patients answer seven standardized questionnaires assessing pain, quality of life and catastrophizing. Bone turnover biomarkers and inflammatory cytokines are measured in fasting serum samples, and bone innervation is evaluated in diagnostic biopsies. MM patients are invited to a follow-up upon completion of first line treatment. This will be the first deep characterization of pain in MM patients and its correlation with disturbances in bone innervation. Understanding how bone turnover and inflammation correlate to pain in MM is crucial to identify novel analgesic targets for this condition.

## 1. Introduction

Multiple myeloma (MM) is a hematological disorder in which terminally differentiated B-lymphocytes are abnormally cloned in the bone marrow, causing solitary plasmacytomas or spreading systemically to other bones. MM is usually associated with elevated serum or urine levels of paraprotein, while formal disease diagnosis requires the presence of ≥10% myeloma cells in the bone marrow and either end-organ damage (which can present in the form of hypercalcemia, renal insufficiency, anemia or osteolytic bone lesions) or a defined biomarker of malignancy [1]. Patients frequently develop myeloma bone disease as a consequence of increased osteoclast-mediated bone resorption and decreased osteoblastic bone formation, which often leads to the development of characteristic focal osteolytic lesions [2]. In most patients, MM is preceded by monoclonal gammopathy of undetermined significance (MGUS), which is characterized by elevated serum paraprotein and <10% myeloma cells in the bone marrow in the absence of end-organ damage [1]. MGUS affects 2%–5% of the population above 50 years of age, with a higher incidence in men, and it is estimated to evolve into MM in a stable rate of 1% per year [3].

While MGUS is considered an asymptomatic disorder, pain is a main cause of physician consultation in MM patients [4], and is more common in MM than in any other hematological cancer [5,6]. In a multi-center study collecting data from MM patients at any disease stage across 18 hematological clinics in the UK, 71% of myeloma patients reported pain (second most common symptom after fatigue, which affected up to 87%), which was described as “severe” or “overwhelming” by approximately 13% [7]. Pain is a feared symptom in cancer patients [8], that impairs their mood [9] and quality of life (QoL) [10]. Moreover, fear of pain has been found to predict up to 11% of the functional limitations of patients suffering from advanced cancer stages [8].

MM is commonly considered a disease of the elderly, as age is an important risk factor for its development [11]. Importantly, it has been shown that QoL is one of the primary concerns in elderly cancer patients, who often find it more important to improve their QoL than their overall survival [12]. Therefore, incorporating measures of pain and QoL in studies assessing clinical interventions for the treatment of MM is of utmost importance. Pain in MM can be grossly classified as either bone pain, arising as a consequence of disease progression; chemotherapy-induced neuropathic pain, as a side effect of the main anti-myeloma medications commonly used to treat the disease, or procedural pain, derived from the invasive medical procedures conducted to treat the myeloma. However, despite the growing focus on pain management, knowledge on the characteristics and baseline presentation of pain and QoL in myeloma patients is scarce. Moreover, the underlying mechanisms of myeloma-induced bone pain are grossly understudied. In preclinical MM models displaying pain-related behaviors, both bone denervation [13] and nerve sprouting [14] of the bone marrow have been described; however, it remains unknown whether this reflects the clinical landscape. Therefore, clinical studies addressing changes in bone innervation in MM patients and their correlation to pain may shed some light on the mechanisms of myeloma-induced bone pain, and bone cancer pain in general.

As novel therapies are being developed, a growing subset of patients live with myeloma as a long-lasting disease, alternating between phases of clinical remissions and relapses. Thus, understanding and improving the pain and subsequent QoL of myeloma patients has become increasingly important. The aim of this study is to provide a deep characterization of the perception of pain and QoL in firstly diagnosed MM patients. Because pain is a subjective, multidimensional experience that comprises sensory, emotional and cognitive dimensions, this study aims to collect patient information through a constellation of standardized, validated questionnaires; data from MM patients will be compared with that from patients receiving a negative myeloma diagnosis (presumably MGUS patients). To further understand the mechanisms of myeloma-induced bone pain, bone innervation and serum inflammatory and bone turnover biomarkers will be evaluated in MM patients and compared with patients with a negative myeloma diagnosis. Moreover, data from MM patients at diagnosis will be compared with data collected upon completion of first-line treatment, and correlations between pain, bone innervation and serum biomarkers will be investigated.

## 2. Research Methods and Analyses

### 2.1. Study Design and Setting

A prospective, observational study in a cohort of patients undergoing a diagnostic bone marrow biopsy for suspected MM. This is a single-center study within an international collaboration; patients will be recruited and samples obtained at Sheffield Teaching Hospital NHS Foundation Trust, Sheffield, UK. Sample analyses will be performed at University of Copenhagen, Copenhagen, Denmark, or University of Southern Denmark, Odense, Denmark. The Danish Association for Multiple Myeloma was contacted during conceptualization; they confirmed the study’s relevance to MM patients. A flow diagram of the study design can be found in Figure 1.

The primary study aims are:To provide a deep characterization of the subjective experience of pain (including pain type, location and severity) and QoL in MM patients at diagnosis, compared to patients with a negative myeloma diagnosis (control group, presumably MGUS patients).To evaluate disturbances in bone innervation (presence, location and density of nerve fibers innervating the bone) in MM patients at diagnosis, compared to patients with a negative myeloma diagnosis.

Secondary aims of this study include evaluating the levels of bone turnover biomarkers and serum inflammatory cytokines in MM patients at diagnosis, compared to patients with a negative myeloma diagnosis.

Additionally, data on pain parameters and QoL, bone innervation and serum biomarkers from MM patients at diagnosis will be compared with data collected following first-line treatment. Correlations between pain and disturbances in bone innervation and serum biomarkers in MM patients before and after treatment will also be investigated.

### 2.2. Study Population

All patients undergoing a diagnostic bone marrow biopsy for suspected MM between October 2019 and June 2021 will be invited to participate by their Hematology Consultant during their scheduled medical appointment. Inclusion and exclusion criteria are specified in Figure 2. Due to the impact of the COVID-19 pandemic on healthcare institutions, the study was paused between March 2020 and August 2020; thus, patient recruitment is expected to continue until June, 2021. The study population will comprise all consenting patients undergoing a diagnostic bone biopsy for suspected MM at Sheffield Teaching Hospital; data from patients with a negative MM diagnosis (confirmed MGUS or smoldering multiple myeloma, SMM, patients) will be used as control. Enrolled patients receiving a positive MM diagnosis will be invited to participate in a study follow-up, upon completion of first-line treatment (approximately 8 months after diagnosis). Patients may withdraw from the study at any point; collected data and tissue will be retained.

### 2.3. Study Objectives

To provide an in-depth characterization of the subjective experience of pain and QoL in MM patients through the completion of standardized questionnaires regarding general pain, bone pain, neuropathic pain, QoL and catastrophizing. Questionnaires from MM patients will be compared with those of patients receiving a negative myeloma diagnosis (control group).To evaluate disturbances in the presence, location and density of sensory and sympathetic nerve fibers innervating the bone marrow of myeloma patients. Biopsies from MM patients will be compared with those of patients receiving a negative myeloma diagnosis (control group).To evaluate changes in the levels of serum biomarkers of bone turnover (carboxy-terminal collagen crosslinks-1, CTX-1, and pro-collagen type 1 N-terminal pro-peptide, P1NP) in MM patients. Levels of bone turnover biomarkers in the serum of MM patients will be compared with those of patients receiving a negative myeloma diagnosis (control group).To evaluate the levels of inflammatory serum cytokines and chemokines in MM patients. Levels of inflammatory biomarkers in the serum of MM patients will be compared with those of patients receiving a negative myeloma diagnosis (control group).To compare data on pain and QoL, bone innervation and serum biomarkers of bone turnover and inflammation in MM patients at diagnosis and following first-line treatment.To evaluate correlations between the self-reported experience of pain and disturbances in bone innervation in MM patients at diagnosis and following first-line treatment.To evaluate correlations between the self-reported experience of pain and serum levels of bone turnover biomarkers in MM patients at diagnosis and following first-line treatment.To evaluate correlations between the self-reported experience of pain and serum levels of inflammatory cytokines in MM patients at diagnosis and following first-line treatment.

### 2.4. Study Procedures

#### 2.4.1. Objectives 1 and 5: In-Depth Characterization of Pain in MM Patients

Patients who consent to participate will receive a booklet with a total of seven standardized questionnaires (Table 1), which will provide a deep characterization of their subjective experience of pain. Data from myeloma patients at diagnosis will be compared with that of patients receiving a negative myeloma diagnosis (control group). MM patients will be asked to complete the same set of questionnaires upon completion of first-line treatment; data from MM patients at diagnosis and following first-line treatment will be compared. The questionnaires include:BPI (Brief Pain Inventory, short version): two-factor questionnaire assessing the severity and interference of pain [15,16]. The severity component assesses location and severity of the pain, as well the analgesic relief provided by current therapy, if any. The interference component is composed by an affective and an activity subdimension. The BPI includes a Visual Analogue Scale (VAS) for assessment of pain intensity, which will be used to establish correlations between pain and disturbances in bone innervation, serum inflammatory and serum bone turnover biomarkers. Data from this questionnaire will allow to draw comparisons between pain severity and interference between MM patients and controls.FACT–BP (Functional Assessment of Cancer Therapy–Bone Pain): Initially developed for the assessment of pain in bone metastases, it measures bone pain and its effect on quality of life. This will provide information on whether myeloma patients suffer from bone pain, compared to controls. Moreover, this questionnaire is sensitive to clinical changes following therapy [17], and will provide important information on whether first-line anti-myeloma treatment improves bone pain and its effect on quality of life in myeloma patients.PCS (Pain Catastrophizing Scale): assessment of the extent of catastrophizing, which is subdivided in three domains: rumination, magnification and helplessness [18]. Mounting evidence suggests that catastrophizing (i.e., enhancing negative, anxiety-inducing thoughts) plays an important role in the subjective experience of pain; to our knowledge, this will be the first data on the role of catastrophizing in myeloma-induced bone pain.EORTC QLQ-C30 (European Organization for the Research and Treatment of Cancer Quality of Life Questionnaire-Core 30): assessment of quality of life in cancer patients. This questionnaire contains a measure of global health status, functional scales (including physical, role, emotional, cognitive and social functioning) and symptoms scales (including fatigue, nausea/vomiting, pain, dyspnea, insomnia, appetite loss, constipation, diarrhea and financial difficulties) [19]. As this questionnaire is widely used to assess the effect of cancer on QoL, it will allow to contextualize the effect of myeloma on QoL in comparison to other cancer types.EORTC MY20 (European Organization for the Research and Treatment of Cancer Quality of Life Questionnaire-myeloma module 20): Supplementary module to administer alongside the EORTC QLQ-C30 for the assessment of disease symptoms, side effects of treatment, future perspective and impact of disease on body image perception [20]. This questionnaire will allow comparisons to other cohorts of myeloma patients.EORTC CIPN (European Organization for the Research and Treatment of Cancer Quality of Life Questionnaire-chemotherapy-induced peripheral neuropathy module): assessment CIPN through a sensory, a motor and an autonomic scale [21]. Administration of this questionnaire at diagnosis will provide baseline data to compare the follow-up data to, allowing the identification of CIPN development after treatment.painDETECT: identification of a possible neuropathic component of pain [22]. This questionnaire, in combination with the EORTC CIPN, will allow the distinction between myeloma-induced neuropathy and chemotherapy-induced peripheral neuropathy”.

Additionally, patients will be asked to fill in a customized demographic questionnaire regarding their marital status, whether they cohabitate with their children, their postal code, country of origin, level of education and employment status. Patients will also be asked to answer the question: “is there any important information regarding your pain experience or quality of life that you feel has not been covered in the given questionnaires?”

Patients will receive the questionnaire booklet during their routine hospital visits, and will be asked to return it in person or mail it back to Sheffield Teaching Hospital, U.K. If a patient consents to participate in the study but feels too unwell to answer the questionnaires on her/his own, a structured interview, in which a researcher asks the questions and notes down the answers, will be offered. Record of self-assessed questionnaires vs. structured interviews will be kept.

#### 2.4.2. Objectives 2 and 5: Immunohistological Characterization of Nerve Fibers Innervating the Bone Marrow in MM

Current guidelines for the diagnosis of MM require the presence of at least 10% clonal cells infiltrating the bone marrow [1]. Therefore, to effectively diagnose MM, the healthcare team routinely extracts diagnostic trephine bone biopsies of the iliac crest and process them for quantification of MM cell infiltration.

Upon finalizing the standard pathology procedures, the research team will access the bone biopsies (both diagnostic and following first-line treatment) and perform an immunohistological characterization of the existence, location and density of neuronal fibers. Bone biopsies from MM patients will be compared to those from patients with a negative myeloma diagnosis. Serial sections will be subjected to multiplex-immunostainings for the pan-neuronal marker PGP9.5 (protein gene product 9.5) combined with the sympathetic nerve fiber marker TH (tyrosine hydroxylase), allowing the distinction between sympathetic and non-sympathetic (presumably sensory) fibers, and the myelinated axon marker NF200 (neurofilament 200), allowing the distinction between myelinated and non-myelinated fibers. A similar protocol for nerve characterization in human bone biopsies has previously been optimized in-house [23]. The analysis will estimate the number of nerve profiles per marrow area (mm^2^) of all PGP9.5-positive nerve profiles and of the nerve fibers’ subtypes, their association with a nerve cluster [23] and the percentage of nerve profiles with another nerve profile within 25 µm. Moreover, the multiplex-immunostaining will be combined with markers for osteoclasts (tartrate-resistant acid phosphatase 5b, TRAcP5b), blood vessels (CD34/CD31) and myeloma cells (CD138), allowing the analysis of the neuronal fibers proximity to blood vessels, myeloma cells and osteoclasts. The analysis will estimate the percentage of nerve profiles with an osteoclast, blood vessel, myeloma cell and bone within 25 µm.

Following first-line treatment, it is standard of care to extract a new bone biopsy to evaluate the presence of malignant plasma cells and assess treatment efficacy. Follow-up biopsies from enrolled MM patients will be analyzed to address the differences in bone innervation at diagnosis and upon completion of first-line treatment. Analyses will be performed by a researcher blinded to patient’s disease diagnosis.

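### The percentage of nerve profiles with a myeloma cell within 25 µm rises with myeloma-cell density, so a raw difference between groups or over time cannot separate spatial association from tumour burden

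*Protocol article*

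**What the plan says.** Section 2.4.2 combines the nerve staining with markers for osteoclasts, vessels and myeloma cells, "allowing the analysis of the neuronal fibers proximity to blood vessels, myeloma cells and osteoclasts". The measure is then fixed: "The analysis will estimate the percentage of nerve profiles with an osteoclast, blood vessel, myeloma cell and bone within" 25 µm. A companion measure is "the percentage of nerve profiles with another nerve profile within 25" µm. Nerve counts are expressed per mm² of marrow. The 25 µm percentages are given no reference to target density and no value expected by chance.

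Two comparisons of the biopsies are planned. Between groups: "Bone biopsies from MM patients will be compared to those from patients with a negative myeloma diagnosis". Over time: "Follow-up biopsies from enrolled MM patients will be analyzed to address the differences in bone innervation at diagnosis and upon completion of first-line treatment". The follow-up biopsy is itself taken to look for remaining malignant plasma cells and judge treatment efficacy.

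The Introduction ties the groups to infiltration. For MM, "formal disease diagnosis requires the presence of ≥10% myeloma cells in the bone marrow", together with end-organ damage or a defining biomarker. MGUS is a condition "which is characterized by elevated serum paraprotein and <10% myeloma cells in the bone marrow in the absence of end-organ damage". Sections 2.2 and 2.4.5 and the Limitations say that controls may be MGUS or SMM patients, and the Limitations say only that controls will often be below 10%.

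**The concern.** A measure of the form *share of points with at least one target inside a fixed radius* mixes two things: how many targets there are, and whether they lie nearer to nerves than chance would put them. Only the second is spatial association. For myeloma cells, the first is close to the grouping variable at baseline and close to treatment response at follow-up.

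The location of nerve fibres is part of the second primary aim (Section 2.1), and the proximity percentages are among its main stated measures. The Discussion expects the position of osteoclasts and plasma cells relative to nerves to help explain the peripheral mechanisms of pain. A raw difference that partly restates the diagnosis would be weak evidence for that. Objective 6 carries the problem further: if the proximity percentage is among the innervation measures correlated with pain, a correlation could reflect tumour burden. Blinding the assessor to diagnosis does not remove the effect, because it lies in the measure and not in the reading. The Limitations do not mention it.

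**Working it through.** **The plan's own figures.** The article gives no figure for the 25 µm measures. Its one computed figure is 17 per group for pain (difference 2.75, SD 2.75, power 80%). Assuming a two-sided alpha of 0.05, which is not stated, the two-sample t-test gives 16.7, hence 17. That number is used below only as the group size.

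**Inputs from the article.** Radius 25 µm (Section 2.4.2); infiltration of at least 10% for MM and less than 10% for MGUS (Introduction).

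**Assumed, not in the article.** Marrow cells per mm², the infiltration values within each group, the number of nerve profiles per biopsy, and the degree of clumping.

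**Step 1: chance percentage.** If targets are placed at random with density λ per mm², then P(at least one within r) = 1 − exp(−λπr²). With r = 0.025 mm, πr² = 0.0019635 mm². For 2,000 cells per mm² and 5% infiltration, λ = 2,000 × 0.05 = 100 and P = 1 − exp(−0.196) = 17.8%.

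| Marrow cells per mm² (assumed) | 5% infiltration | 10% | 40% |
|---|---|---|---|
| 2,000 | 17.8% | 32.5% | 79.2% |
| 4,000 | 32.5% | 54.4% | 95.7% |
| 6,000 | 44.5% | 69.2% | 99.1% |

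None of these values contains any nerve-myeloma association. A direct spatial simulation at λ = 200 gave 33.4%, against 32.5% from the formula.

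**Step 2: consequence for the comparisons.** Simulation of 17 versus 17 patients with no association, 20 nerve profiles per biopsy and 1,000 to 5,000 cells per mm². Infiltration was 1-9% in MGUS, 10-60% in MM and 0-5% after treatment. Cells were single or in clumps of 10, with each clump counted as one target. In a variant, about half the controls were SMM at 10-30%.

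- At 2,000 per mm² with single cells and MGUS controls, mean percentages were about 18% in controls, 70-71% in MM and 9% after treatment. The raw comparisons were significant in every run.
- With about half the controls SMM, the means were 35% versus 71%, and 99% of runs were significant.
- Weakest case (1,000 per mm², clumps of 10, about half SMM): 2.4% versus 6.6%, significant in 64% of runs.
- Over all scenarios, the raw percentage was significant in 64-100% of runs between groups and 99-100% before versus after.

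**Step 3: with a chance reference.** Observed minus the percentage at 1,000 random points per biopsy was significant in 4.3-5.8% of runs in every scenario, near the nominal 5%. In these runs the nerves were also placed without structure, so this does not test the correction against real marrow anatomy.

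**Step 4: other targets.** The dependence on the amount of target also holds for osteoclasts, vessels, bone and neighbouring nerve profiles. The Introduction reports increased osteoclast-mediated resorption in MM but no osteoclast counts, and the article gives no group difference in vessel, bone or nerve density.

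**The case against.** Several points on the other side are fair.

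- *The raw percentage is a legitimate quantity.* The Discussion hypothesises that tumour injures nerves. On that view the share of nerve profiles with a myeloma cell nearby measures exposure, however the closeness arises. This stands, and is why the raw value should be kept.
- *The article states no interpretation of this measure.* A reader might infer that the authors will report a higher percentage as attraction between nerves and tumour, or a fall after treatment as nerve remodelling. Neither is written. What is written is that proximity will be analysed, that the biopsies will be compared both ways, and that the findings bear on mechanism. That is enough to need a measure able to support the conclusion.
- *A fuller plan may hold a correction.* Possible. But the article does not leave the measure open; it fixes it as a plain percentage, while it does scale nerve counts by area.
- *The group gap is not fixed.* True. MM needs more than infiltration, so a patient with a negative diagnosis can have 10% or more, and SMM patients are among the controls.
- *Uniform random points are a crude reference.* Also true. The Discussion reports, from primary hyperparathyroidism patients, that most nerve profiles lie close to vessels and that density is higher above remodelling surfaces. A uniform reference could show nerve-osteoclast or nerve-bone association that only reflects this anatomy. The fix has to allow for it.

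**Conclusion.** The point holds for the myeloma-cell percentage. The measure as fixed rises with tumour burden, and both planned comparisons are tied to tumour burden, so a raw difference is expected in part without any spatial association. By chance alone the percentage is about 18-45% at 5% infiltration and 33-69% at 10%, assuming 2,000 to 6,000 marrow cells per mm² and random placement. The direction does not depend on those assumptions; the size does. SMM controls, clumping and poor response all narrow the difference.

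Two stronger readings are tempting and not supported. One is that MM must differ from controls on every proximity percentage: for osteoclasts, vessels, bone and neighbouring nerves the article establishes no difference in density. The other is that the second primary aim fails as a whole: nerve profiles per mm² are unaffected, and the raw percentages remain valid as exposure or description.

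**What to change.** Add to Section 2.4.2, before the biopsies are analysed:

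1. Keep the raw 25 µm percentages, reported as exposure, with the target density of each biopsy beside them.
2. For each biopsy, apply the same 25 µm rule to many random points in the marrow area of the same section. The resulting percentage is the value expected by chance.
3. Base any conclusion about nerve-target proximity, between groups, over time or in correlation with pain, on observed minus expected, with one value per patient and biopsy.
4. As a sensitivity check, restrict the random points to match the known closeness of nerves to vessels and bone surfaces, or adjust for target density. Where vessel or bone is itself the target, use the density adjustment, since matching on it would remove the quantity of interest.

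Cost: some extra image-analysis work on the stained sections. The article does not say that coordinates are stored, so they may have to be extracted. No new staining and no new patients are needed.

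### Blinding the biopsy reader to diagnosis alone is at risk from the CD138 stain in the MM-versus-control comparison, and gives no protection in the before-after and pain-correlation analyses

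*Protocol article*

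**What the plan says.** All of the following is in section 2.4.2 of the protocol article unless another section is named.

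- **Blinding.** The only statement is "Analyses will be performed by a researcher blinded to" the patient's diagnosis. It closes the paragraph on follow-up biopsies. Time point and pain score are not mentioned.
- **Nerve measures.** "Serial sections will be subjected to multiplex-immunostainings for the pan-neuronal marker PGP9.5", together with TH and NF200. From these, "The analysis will estimate the number of nerve profiles per marrow area", overall and by fibre subtype, plus association with a nerve cluster and nerve-to-nerve distance.
- **Added markers.** A further step is that "the multiplex-immunostaining will be combined with markers for osteoclasts", for blood vessels, and for "myeloma cells (CD138), allowing the analysis of the neuronal fibers proximity to blood vessels, myeloma cells and osteoclasts". The resulting measure is the "percentage of nerve profiles with an osteoclast, blood vessel, myeloma cell and bone within 25 µm".
- **Comparisons.** Innervation in MM patients against patients with a negative diagnosis is the second primary aim (section 2.1). Objective 5 compares MM patients at diagnosis and after first-line treatment. Objective 6 correlates innervation with self-reported pain in MM patients (section 2.3).
- **What defines the groups.** Diagnosis of MM needs at least 10% clonal cells in the marrow. The Introduction adds that end-organ damage or a biomarker of malignancy is also required. The limitations section says that controls, with MGUS or smoldering myeloma, will often have less than 10% malignant plasma cells, and that MGUS patients may carry low levels of clonal cells.

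**The concern.** The blinding sentence promises one thing, ignorance of diagnosis, and the staining described beside it works against that promise. A reader who sees the CD138 signal sees the quantity on which the diagnosis partly rests, and need not be told the group in order to guess it.

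The scope is the second difficulty. Innervation enters three analyses, and in two of them diagnosis does not vary, so being blind to it shields nothing.

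What is at stake is one of the two primary aims and the two analyses built on it. Recognising nerve profiles, assigning subtypes and calling clusters can involve judgement. The investigators also hold expectations: the Discussion hypothesises that nerve injury may cause the pain, and the limitations section anticipates finding nerve disturbances in these biopsies. A reader who can tell the groups, or the two time points, apart could create, enlarge or hide a difference.

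**Working it through.** **Step 1. Set the blinding statement against each innervation analysis.**

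| Analysis | Who is compared | Does diagnosis vary? | What has to be masked | Covered by the sentence? |
|---|---|---|---|---|
| Second primary aim (Objective 2) | MM against MGUS/smoldering myeloma | Yes | Diagnosis | Yes, but CD138 may reveal it |
| Objective 5 | MM patients, at diagnosis and after treatment | No | Time point | No |
| Objective 6 | Within MM patients, across pain scores | No | Pain score | No |

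The stated blinding addresses one of the three, and the stain weakens it for that one.

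**Step 2. Sort the measures by whether they need CD138.**

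- Not needed: profiles per mm², subtypes, cluster association, nerve-to-nerve distance within 25 µm.
- Not needed: distance to osteoclasts, vessels or bone.
- Needed: share of nerve profiles with a myeloma cell within 25 µm.

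Only the last measure cannot be scored without seeing CD138. For the others, exposure depends on whether the channels are displayed together, or on which of the serial sections carries CD138. The article states neither.

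**Step 3. Ask how much CD138 reveals.** MM requires at least 10% clonal cells, and controls will often have less, so the amount of staining points to the group. It does not settle it, because controls may carry clonal cells and MM needs a further criterion.

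**Step 4. Give a scale.** The article has no figure from which the bias could be derived. Its only design figure is 17 per group for worst pain on the BPI (section 2.4.5). That figure reproduces. With a difference of 2.75 and an SD of 2.75 the standardised difference is 1. With two-sided alpha 0.05 (assumed, since the article does not state alpha) a two-sample t-test needs 16.71 per group, rounded up to 17, with power 80.7% at 17. It was not calculated for nerve density and is borrowed here only as a group size.

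Assume no true difference and a reader who shifts one group by δ SD:

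- Noncentrality = δ × √(n/2). For δ = 0.3 and n = 17: 0.3 × √8.5 = 0.875.
- Normal approximation: 1 − Φ(1.96 − 0.875) + Φ(−1.96 − 0.875) = 0.139 + 0.002 = 0.141.
- t-test with 32 degrees of freedom: 0.136.

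| Assumed shift (SD) | False-positive rate, t-test |
|---|---|
| 0 | 5.0% |
| 0.2 | 8.7% |
| 0.3 | 13.6% |
| 0.5 | 29.3% |

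Every shift in this table is an assumption.

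**The case against.** **The tempting stronger reading.** A reader might infer that the promised blinding is simply not delivered for the second primary aim. The article does not show that. Presence and density come from the nerve markers alone, and only part of location uses CD138. Nothing says that all channels are in view while nerves are counted, and serial sections leave open which section carries CD138. CD138 suggests the diagnosis without fixing it, and the reader can remain unaware of the diagnosis label, which is all that the sentence claims. This part of the objection stands and limits the point to a risk.

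**Reading procedure belongs in the full protocol.** Display order, image coding and reading order are commonly left out of a journal article, and section 2.4.2 refers to an earlier in-house staining protocol. This is fair for the mechanics, and their absence alone would be no finding. But the article chose to state what the reader is blinded to, and that stated scope does not fit two of its own comparisons.

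**Nothing suggests that the reader sees pain scores.** Data are pseudonymised to a study code (section 4), patients are recruited in Sheffield and samples are analysed in Denmark (section 2.1). That lowers the risk for Objective 6, but it is not a statement of masking.

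**No direction of bias follows.** Nerve injury and nerve sprouting are opposite changes, and the article says it is unknown whether either occurs in patients. This stands: the direction of any reader bias cannot be predicted.

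**Conclusion.** The point holds as a risk and a mismatch of scope. For the MM-versus-control comparison, blinding to diagnosis is at risk and no described step protects it. Myeloma-cell proximity cannot be fully blinded under any reading procedure, because its scoring needs the CD138 signal. For the before-after comparison and the pain-innervation correlation, blinding to diagnosis has no effect, since every patient has MM. This second part does not depend on how the channels are displayed.

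The size of any bias is unknown. The figure of about 14% false positives rests on an assumed 0.3 SD shift, 17 per group, two-sided alpha 0.05 and no true difference. It shows only that a modest shift would matter at this sample size. The change is worth making because it is cheap and bears on a primary aim.

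**What to change.** Replace the blinding sentence in section 2.4.2 with one that masks the reader to diagnosis, time point and pain scores, and state a two-step reading.

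1. Identify, subtype and count nerve profiles on coded images in random order, with diagnostic and follow-up biopsies mixed. Show only the PGP9.5, TH and NF200 channels, or use a section without CD138. Lock the coordinates.
2. Then open the CD138, TRAcP5b and CD34/CD31 channels and score proximity from the locked coordinates, by software where possible.

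Add a sentence acknowledging that myeloma-cell proximity cannot be fully blinded.

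Cost: a change of wording and reading order, with the same reader, slides and patients. Images are opened twice, and marrow morphology may still hint at infiltration, so masking in step 1 will be better but not perfect.
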